**Figure 2 F2:**
[figure not shown]
Study flow. PM = particulate matter.

### Data collection

2.4

The participants’ demographics and clinical data, including age, sex, body mass index, smoking status, medical history (including asthma), and exacerbation history will be obtained at enrolment. The participants will visit their respective hospitals every 3 months for 1 year. At each visit, the participants will perform pre- and postbronchodilator spirometry. Their COPD assessment test, modified Medical Research Council, and St. George Respiratory Questionnaire for patients with COPD scores will be obtained to assess respiratory symptoms and health-related quality of life. Development of acute exacerbation will be checked monthly via a telephone interview and/or at the regular follow-up visit. Any changes in inhaler medications or hospitalizations for respiratory causes will be monitored. Sputum samples will be obtained at each visit and blood samples, at the end of the study. The timeline of data collection is shown in Table 1.

**Table 1 T1:** Timeline of data collection.

	Screening	Visit 1	Visit 2	Visit 3	Visit 4
	0 mo	3 mo	6 mo	9 mo	12 mo
Clinical data					
PFT	+	+	+	+	+
CAT, mMRC	+	+	+	+	+
SGRQ	+	+	+	+	+
Exacerbation	Monthly				
Individual environmental risk assessment					
Residence	+				
Activity		+	+	+	+
Protective behavior	+	+	+	+	+
Indoor PM measurement					
Gravimetric method		+		+	
Light scattering method		+	+	+	+
Portable device		+	+	+	+
IoT-based device	Continuous monitoring				
Outdoor PM measurement					
IoT-based device	Continuous monitoring				
Air pollution network	Continuous monitoring				
Samples					
Sputum		+	+	+	+
Blood					+

#### Residential environment assessment

2.4.1

Study participants will complete a detailed questionnaire about their residential environment at enrolment. The outdoor environmental assessment will include the following: the location of their current residence; distance from the road; traffic volume; and time spent outside of the house at weekdays and weekends. Collected information on their indoor environment will include the following: type of housing; year of construction; number of family members residing together; number of rooms; methods for heating and cooling; methods of indoor ventilation; presence and types of household appliances (air cleaner, air conditioner, humidifier, dehumidifier, gas heater, oil-filled heater, and fireplace); air cleaner operating time; whether the kitchen and living room are separated; use of ventilating fan when cooking; type of flooring; presence of curtains; presence of sofa and type of material; presence of mold; whether participants have recently moved; any renovation or reconstruction works; presence and type of pet; presence and type of plants; methods of cleaning and frequency; and exposure to indoor secondhand smoking.

#### Indoor and outdoor PM exposure assessment

2.4.2

“Internet-of-things (IoT)”-based PM measuring devices (CP-16-A5; Aircok Inc., Seoul, Republic of Korea) will be installed inside and outside of the house for year-round monitoring of indoor and outdoor PM concentration levels. Gravimetric and light-scattering methods will also be performed for more precise indoor PM measurement. A mini-volume air sampler (Model KMS-4100; KEMIK Corp., Seongnam, Republic of Korea), MicroPEM (RTI International, Research Triangle Park, NC), and dust spectrometer (11-D; GRIMM Aerosol Technik Ainring GmbH & Co. KG, Ainring, Germany) will be installed at the participants’ homes for 24 hours every 3 months. The devices will be installed in the room the participant reportedly spend the most time in. When these devices are installed, the participants will be asked to record a time-activity diary and carry a portable PM measurement device (Airbeam2; HabitatMap, Inc., Brooklyn, NY) to assess their time spent indoors and outdoors and to estimate individual exposure to PM. Outdoor measurement from the IoT-based device will be complemented with the information from Air Korea, a national air pollution information system in the Republic of Korea (http://www.airkorea.or.kr) that provides data on the PM concentrations relating to the residential address.

#### Statistical estimation for unmeasured PM exposure

2.4.3

Although outdoor PM concentrations will be measured with the aforementioned devices, it will be necessary to estimate individual exposures not identified during the actual measurement period. For this, land use regression (LUR) modeling, a popular method for exposure estimation, will be applied.^[16–18]^ LUR models incorporate monitoring data and land-use variables, such as road type, traffic volume, population density, altitude, and topography data obtained using Geographic Information Systems. The LUR modeling that will be used for this study was described in a previous study.^[19]^ The microenvironmental modeling (Stochastic Human Exposure and Dose Simulation) will be applied to estimate distributions of microenvironmental PM concentrations and exposures for participants (Fig. 4).^[20]^

### Study outcomes

2.5

We will investigate if the behavioral interventions reduce the degree of PM exposure and result in improved clinical outcomes compared with the usual care. The study outcomes are risks of acute exacerbation, respiratory-related hospitalization, death, difference in FEV_1_ from the baseline, and changes in the COPD assessment test, modified Medical Research Council, and St. George Respiratory Questionnaire for patients with COPD scores. The study concept is illustrated in Figure 3.

**Figure 3 F3:**
[figure not shown]
Study concept. This study aims to evaluate the efficacy of behavioral interventions to reduce PM exposure and its effect on the clinical outcomes of patients with COPD. We will examine if the behavioral interventions are associated with a reduction in individual PM exposure and ultimately with improved clinical outcomes. COPD = chronic obstructive pulmonary disease, IoT = internet-of-things, mMRC = modified Medical Research Council, PM = particulate matter.

**Figure 4 F4:**
[figure not shown]
Individual PM exposure estimation. The individual PM exposure estimation will be performed based on the concept of the Stochastic Human Exposure and Dose Simulation model. GPS = global positioning system, LUR = land use regression, PM = particulate matter.

### Statistical analysis

2.6

Data will be analyzed using SAS software (SAS Institute Inc., Cary, NC) and R software (version 3.5.2; R Development Core Team, Vienna, Austria). Data will be presented as means ± standard deviation or median [interquartile range] for continuous variables and percentages for categorical variables. The Student *t* test or Mann–Whitney test will be used for continuous variables, and the chi-squared test and Fisher exact test will used to compare categorical variables. *P*-values of <.05 will be considered of statistical significance. The risk of acute exacerbation and the incidence of respiratory hospitalization will be compared in the intervention group and the non-intervention group (Chi-squared test or Fisher exact test).

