### Study design

2.1

This study is a multicenter randomized controlled trial evaluating the efficacy of behavioral interventions to reduce PM exposure in patients with COPD. A total of 120 patients will be enrolled from 3 academic institutions located in the capital region of the Republic of Korea (Fig. 1): 60 from Asan Medical Center (Seoul), 30 from Severance hospital (Seoul), and 30 from Ilsan Paik Hospital (Goyang). The study duration is 1 year and study participants will be followed up on every 3 months after a screening visit. This study was approved by the Institutional Review Board of each site: Asan Medical Center (2021-0701), Severance Hospital (4-2021-0607), and Ilsan Paik Hospital (2021-05-042). All of the participants will be asked to provide their written informed consent after receiving comprehensive information about the study. Additional informed consent will be obtained for the collection and use of biological specimens.

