### Randomization and intervention

2.3

The study flow is shown in Figure 2. After enrolment, indoor PM_2.5_ concentrations will be measured for 1 month for each participant (baseline indoor PM_2.5_ concentrations). Study participants will be randomly allocated (1:1) either to the intervention group or the usual care group using the baseline monthly PM_2.5_ concentrations and baseline FEV_1_. The behavioral interventions will comprise the following 5 activities: checking the air quality forecast; operating an indoor air cleaner and regular check-up of filters; ventilating their home regularly by opening windows; adhering to inhaler treatment; and refraining from going out on high air pollution days. The intervention group will receive education at each visit on the importance of their behavioral change and will be advised to complete checklists everyday as part of their compliance with the interventions. Air cleaners will be rented to participants in the intervention group during the study period if they do not have one. The usual care group will continue to receive the treatment they were receiving but without any instructions on behavioral changes.

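### FEV1, CAT and SGRQ changes are to be compared by a t or Mann–Whitney test with no covariate adjustment and no stated use of the four follow-up visits: valid, but less precise than the data allow

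*Protocol article*

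**What the plan says.** Section 2.5 (Study outcomes) of the protocol article defines the continuous clinical outcomes as changes: "difference in FEV_1_ from the baseline, and changes in the COPD assessment test, modified Medical Research Council, and St. George Respiratory Questionnaire".

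Section 2.4 (Data collection) sets the schedule: "The participants will visit their respective hospitals every 3 months for 1 year", and "At each visit, the participants will perform pre- and postbronchodilator spirometry". Table 1 marks lung function, CAT, mMRC and SGRQ at screening and at 3, 6, 9 and 12 months, so each has one baseline and four later values.

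Section 2.3 (Randomization and intervention) says that participants are allocated "using the baseline monthly PM_2.5_ concentrations and baseline FEV_1".

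Section 2.6 (Statistical analysis) gives the method: "The Student *t* test or Mann–Whitney test will be used for continuous variables". This sentence is generic and does not name FEV1 or any score. It governs them because the section offers nothing else for continuous variables: no covariate, no longitudinal model and no target visit.

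**The concern.** A two-sample test takes one number per patient. The trial will hold five values per patient for each of these outcomes, and it uses two baseline variables in the allocation. The stated method uses the baseline only by subtracting it, sets the allocation variables aside, and does not say which follow-up value or summary is tested.

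Subtracting the whole baseline is the best use of it only when the baseline–follow-up correlation is 1. Below that, regressing the follow-up on the baseline gives a smaller variance. Balancing the arms on a prognostic variable and then leaving it out of the analysis also tends to make the reported standard error too large. With 120 patients in total, precision that costs only analysis wording is worth keeping.

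**Working it through.** **Inputs from the protocol article.** Total 120 patients (Section 2.1); four post-baseline visits (Section 2.4 and Table 1); outcomes defined as changes (Section 2.5); significance level 0.05 (Section 2.6), taken as two-sided because sidedness is not stated. The article gives no effect size, standard deviation, power or dropout, so the figure of 120 cannot be reproduced. The abstract gives 2:1 allocation and Section 2.3 gives 1:1. That is a separate matter: the ratios below are the same for 60/60 and 80/40.

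**Assumptions.** Equal variance at all visits (set to 1) and correlation rho between baseline and follow-up. The documents give no rho, so a range is shown. For the visit average, the same rho is assumed between every pair of visits (compound symmetry).

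**Target A: one visit, for example 12 months.**
- Change score: variance 1 + 1 − 2·rho = 2(1 − rho).
- Follow-up adjusted for baseline: 1 − rho² = (1 − rho)(1 + rho).
- Ratio: (1 + rho)/2.

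**Target B: average over the four visits.**
- The mean of four visits has variance (1 + 3·rho)/4 and covariance rho with the baseline.
- Mean change: (1 + 3·rho)/4 + 1 − 2·rho = 1.25(1 − rho).
- Mean adjusted for baseline: (1 + 3·rho)/4 − rho² = (1 − rho)(1 + 4·rho)/4.
- Ratio: (1 + 4·rho)/5.

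**Results.** The third column is 120 × (1 + rho)/2. The fourth is the power of the adjusted test when the effect is set so that the change-score t test has 80%: Φ[(1.960 + 0.842)/√ratio − 1.960].

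| rho (assumed) | A: variance ratio | A: N matching 120 | A: power instead of 80% | B: variance ratio |
|---|---|---|---|---|
| 0.5 | 0.75 | 90 | 89.9% | 0.60 |
| 0.6 | 0.80 | 96 | 87.9% | 0.68 |
| 0.7 | 0.85 | 102 | 86.0% | 0.76 |
| 0.8 | 0.90 | 108 | 84.0% | 0.84 |
| 0.9 | 0.95 | 114 | 82.0% | 0.92 |
| 0.95 | 0.975 | 117 | 81.0% | 0.96 |

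**Allocation variables.** Suppose, as an illustration, that the allocation balances baseline FEV1 almost perfectly. The difference in FEV1 change then already has variance of about 1 − rho², but the t test still computes its standard error from 2(1 − rho). Its real two-sided error rate is 2·[1 − Φ(1.960/√((1 + rho)/2))], about 2.8%, 3.4% and 4.4% at rho 0.6, 0.7 and 0.9, against a nominal 5%. In that case the loss for FEV1 shows as an inflated standard error rather than a noisier estimate, and adjustment removes it.

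**The case against.** The strongest reply is that this is a condensed article. Covariates, target visit, covariance structure and missing-data rules commonly sit in the full protocol or SAP, which are not shown, and their absence here is no fault. That stands for those details. It does not cover the test itself, which the article names as its method for continuous variables. If a fuller document holds a longitudinal model, Section 2.6 misdescribes it and should be aligned.

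Four stronger readings are tempting, and the documents do not support them.

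- **That the baseline is unused.** Section 2.5 defines the outcomes as changes, so the baseline enters by subtraction. It is missing only as a covariate.
- **That the plan tests visit by visit and drops patients who miss a visit.** Section 2.6 says neither. A t test could be applied to each patient's mean change or slope, and the Discussion speaks of lung function decline. What can be said is that the use of the visits is not stated.
- **That a mixed model is worth roughly 1.7 to 2.4 times the sample.** That figure sets an adjusted four-visit average against an unadjusted 12-month change: the ratio is (1 + 4·rho)/8, or 0.425 to 0.575 for rho 0.6 to 0.9. The targets differ. A plain t test on the averaged change already has 1.25/2 = 0.625 of the 12-month variance, with no model at all. The figure also needs an equal effect at every visit. Education is repeated at each visit, and if benefit builds up, averaging dilutes it.
- **That chance baseline imbalance threatens the FEV1 comparison.** The allocation uses baseline FEV1, so the design addresses this. The argument has more force for CAT and SGRQ, which the allocation does not use.

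It is also fair that for a 12-month target with complete data a repeated-measures model adds little beyond simple baseline adjustment. Its main benefit there is in handling missed visits.

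**Conclusion.** The point holds as a loss of efficiency. The comparison is valid under randomization, and nothing here shows bias.

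For a single-visit target the variance saved by baseline adjustment runs from 25% at rho 0.5 to 2.5% at rho 0.95. If FEV1 is highly correlated over a year (rho 0.8 to 0.95), the saving is 10% down to 2.5%, which is modest. Scores with lower correlation would gain more. For a visit-averaged target the like-for-like saving is 32% to 8% for rho 0.6 to 0.9, equivalent to about 1.47 to 1.09 times the sample (1/0.68 and 1/0.92).

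These sizes rest on assumed correlations, equal variances and, for the average, compound symmetry. The direction does not depend on the value of rho: under these assumptions the change-score test is never the more precise of the two. The change is worth making because it is nearly free, even where the gain is small.

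**What to change.** In Section 2.6, replace the generic test for FEV1, CAT and SGRQ with a baseline-adjusted repeated-measures model on all post-baseline visits. Fixed effects: arm, visit, arm-by-visit, the baseline value of the outcome, and the allocation variables baseline PM2.5 and baseline FEV1. When FEV1 is the outcome, enter its baseline only once. State in advance whether the target is the 12-month difference or the visit average, and report the adjusted difference with its 95% confidence interval. If the full protocol or SAP already contains such a model, bring Section 2.6 into line with it.

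The cost is slightly more analysis work and explanation than a t test needs. No visit, measurement or patient is added, and SAS and R are already named.

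### Acute exacerbation is compared by an unadjusted test although exacerbation history is collected at enrolment and is not an allocation factor: a valid test, with a modest and avoidable loss of precision

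*Protocol article*

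**What the plan says.** Four places in the protocol article bear on this point.

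- **Data collection (2.4):** "medical history (including asthma), and exacerbation history will be obtained at enrolment".
- **Randomization and intervention (2.3):** patients are allocated "using the baseline monthly PM_2.5_ concentrations and baseline FEV_1". Exacerbation history is not named as a factor.
- **Study outcomes (2.5):** "The study outcomes are risks of acute exacerbation, respiratory-related hospitalization, death, difference in FEV_1_ from the baseline", followed by the symptom and quality-of-life scores.
- **Statistical analysis (2.6):** "The risk of acute exacerbation and the incidence of respiratory hospitalization will be compared in the intervention group and the non-intervention group", with the method given in brackets as "Chi-squared test or Fisher exact test".

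The trial is small: "A total of 120 patients will be enrolled from 3 academic institutions". The article nowhere uses exacerbation history in allocation, stratification or adjustment.

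**The concern.** A patient's exacerbation history is the baseline version of the exacerbation outcome, and patients with a history can be expected to exacerbate more often. The design already treats prognostic balance as important, since it allocates on FEV1. For exacerbation, however, it leaves the most direct baseline predictor to chance and then uses a test that cannot take a covariate.

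Two things are at stake. Variation in the outcome that history could explain stays in the error term. And if the arms happen to differ in the share with a history, the crude risk difference carries that gap. Any adjustment brought in after the baseline table has shown the gap would be post hoc.

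**Working it through.** **Inputs from the article.** N = 120. The arms are 60/60 under the 1:1 ratio in section 2.3, or 80/40 under the 2:1 ratio in the Abstract. Both are carried through, and the choice does not alter the conclusion. The significance level is 0.05, taken as two-sided. The article gives no event rate, effect size or power, so there is no stated figure to reproduce.

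**Assumptions, not in the article.** History is coded none vs at least one. Its prevalence is p = 30-50%. The control-arm one-year exacerbation risk is r1 = 50-70% with history and r0 = 25-30% without. The treatment effect is an odds ratio of 0.4 or a relative risk of 0.55.

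**1. Chance imbalance.** The SD of the between-arm difference in the share with history is √[p(1−p)(1/n1 + 1/n2)].
- 60/60, p = 0.3: √(0.21 × 2/60) = 0.084.
- 80/40, p = 0.5: √[0.25 × (1/80 + 1/40)] = 0.097.

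The exact binomial probability of a gap of 10 points or more is 27-33% across the two ratios. Counting only gaps strictly above 10 points gives 20-27%.

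**2. Effect of a 10-point gap on the crude risk difference.** The shift is 0.10 × (r1 − r0): 0.10 × 0.20 = 2 points for 50% vs 30%, up to 0.10 × 0.45 = 4.5 points for 70% vs 25%.

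**3. Variance explained.** R² = p(1−p)(r1−r0)²/[m(1−m)], with m = p·r1 + (1−p)·r0. The equivalent extra sample is 120/(1−R²) − 120.
- p = 0.3, 50% vs 30%: m = 0.36; R² = 0.21 × 0.04/0.2304 = 0.036; about 5 patients.
- p = 0.4, 60% vs 30%: m = 0.42; R² = 0.24 × 0.09/0.2436 = 0.089; about 12 patients.
- p = 0.4, 70% vs 25%: m = 0.43; R² = 0.24 × 0.2025/0.2451 = 0.198; about 30 patients.

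These apply control-arm risks to both arms, which is too generous if the treatment works. At relative risk 0.55 the treated-arm risks in the last case are 38.5% and 13.75%, with m = 0.2365. Pooling the arms, R² = (0.0486 + 0.0147)/(0.2451 + 0.1806) = 0.149, about 21 patients. The 60% vs 30% case falls in the same way to 8.6. A fair range is therefore roughly 5-20.

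**4. Power for exacerbation.** Simulated chi-squared power, then power of a Cochran-Mantel-Haenszel (CMH) test stratified by history, at odds ratio 0.4 (8,000 trials per scenario):

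| Prevalence; risk with vs without history | 60/60 | 80/40 |
|---|---|---|
| 30%; 50% vs 30% | 57.4 → 57.7% | 55.0 → 55.0% |
| 40%; 60% vs 30% | 58.3 → 60.4% | 53.8 → 56.3% |
| 50%; 70% vs 30% | 55.7 → 60.7% | 51.3 → 57.2% |

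Stratifying cuts the variance of the risk difference by about 1-3%, 7-8% and 13-15% in the three rows. At relative risk 0.55, 60/60 and p = 0.4, power goes from 61.0 to 62.8% (60% vs 30%), 63.6 to 66.7% (65% vs 30%) and 62.4 to 67.9% (70% vs 25%).

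**5. Validity.** With no treatment effect, the chi-squared test rejects in 4.5-5.7% of simulated trials. If one looks only at trials in which a given arm has at least 10 points more patients with history, its rejection rate is 7-9% at 60/60 and 6-8% at 80/40 under the stronger contrasts. The stratified test stays near 5%.

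**6. Respiratory hospitalisation.** Assume 40% with history and a risk of 20% vs 5%. The variance cut is about 2-5%. At odds ratio 0.4, power moves from 22.8 to 23.0% (60/60) and from 24.0 to 25.5% (80/40). At relative risk 0.55 and 60/60 it moves from 15.7 to 15.8%. At 80/40, a history-adjusted model with a robust standard error does worse than chi-squared (16.7 down to 10.2%), because events are sparse in the smaller arm.

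**The case against.** The strongest reply is that an unadjusted comparison of randomised arms is unbiased and keeps its error rate, so this is a preference and not a defect. The first half stands. A reader might infer that the planned test is biased or invalid, and neither the article nor the calculations support that. What remains is efficiency and protection against imbalance in the one trial that will be run.

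A second reply is that covariates are usually left to the analysis plan, which is not shown. That holds for supportive models. But section 2.6 gives exacerbation its own sentence and names the test, so the point addresses a stated choice and not a silence.

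Third, the size depends on how prognostic history is, which the article does not say. This stands: at 50% vs 30% the power gain is close to nil. If FEV1 is correlated with history, allocating on FEV1 already removes part of the imbalance, so the imbalance figures lean towards the upper end.

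Fourth, a reader might extend the point equally to respiratory hospitalisation, which shares the sentence and the test. The calculations do not bear that out. With few events, Fisher is a reasonable choice.

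Fifth, the article gives no look-back period or severity for exacerbation history. The none vs at least one coding used here is an assumption that the plan would have to define.

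**Conclusion.** The point holds for acute exacerbation, as a modest improvement. Under the assumed rates, a 10-point or larger imbalance in history arises in roughly 20-33% of trials and shifts the risk difference by 2-4.5 points. Using history gains about 0-6 power points, worth roughly 5-20 patients at N = 120. The figure of 30 patients that control-arm risks alone would suggest does not hold once the treated arm's lower risk is counted. Type I error of the planned test is about 5% over all randomisations. For respiratory hospitalisation the gain is small to negligible. All sizes depend on assumed event rates. The facts that history is collected, is not an allocation factor and is not part of the stated comparison do not.

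**What to change.** Before outcome data are seen by arm, state in section 2.6 that acute exacerbation is compared with stratification by, or adjustment for, exacerbation history at enrolment (none vs at least one), and define the look-back period. One suitable form is a CMH test with a history-standardised risk difference. Keep the chi-squared or Fisher result as supportive. For respiratory hospitalisation, use the stratified CMH or exact form only if event numbers allow, and otherwise keep Fisher.

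The cost is analysis wording only. The variable is already collected, and no visits, patients or procedures are added.

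### The chi-squared or Fisher test named for exacerbation risk uses one yes/no value per patient and ignores the repeat events and time at risk that a year of monthly checks can supply

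*Protocol article*

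**What the plan says.** Section 2.6 (Statistical analysis) names the endpoints and the test together. "The risk of acute exacerbation and the incidence of respiratory hospitalization will be compared" opens the sentence, and it ends with the method: "respiratory hospitalization will be compared in the intervention group and the non-intervention group (Chi-squared test or Fisher exact test". The general rule in the same section assigns t or Mann–Whitney tests to continuous data and chi-squared or Fisher tests to categorical data, with the threshold "values of <.05 will be considered of statistical significance". No count, rate or time-to-event method is named for any outcome.

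Section 2.4 (Data collection) describes richer data. For exacerbations, "Development of acute exacerbation will be checked monthly via a telephone interview and/or at the regular follow-up visit"; Table 1 also marks them as monthly. For admissions, "Any changes in inhaler medications or hospitalizations for respiratory causes will be monitored". Section 2.1 sets the frame: "The study duration is 1 year and study participants will be followed up on every 3 months after a screening visit", and "A total of 120 patients will be enrolled from 3 academic institutions". Exacerbation history is collected at enrolment. Section 2.5 lists exacerbation, respiratory hospitalization and death among several outcomes and ranks none as primary.

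**The concern.** Chi-squared and Fisher tests compare the proportion of patients with at least one event. A patient with five exacerbations counts the same as a patient with one, and length of observation does not enter. An intervention that mainly prevents repeat exacerbations would be largely invisible to this test, and with 120 patients there is little information to spare.

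A second issue is conditional. If a patient who leaves early without an event stays in the denominator as event-free, the arm with shorter follow-up shows fewer patients with events even when the true rates are equal.

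**Working it through.** The article gives no design calculation behind N = 120, so there is no stated figure to reproduce. The document supplies N, one year of follow-up and the 0.05 threshold, taken here as two-sided. Event rate, dispersion, rate ratio and dropout are assumptions. The Abstract says 2:1 and section 2.3 says 1:1, so both 60/60 and 40/80 (usual care/intervention) were tried.

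**Step 1: power with full follow-up.** With yearly rate μ and dispersion k (gamma-Poisson), P(any event) = 1 − (1 + kμ)^(−1/k).

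- Chi-squared power ≈ Φ[(|p_c − p_t| − 1.96·SE0)/SE1], with SE0 pooled and SE1 unpooled.
- Negative binomial power ≈ Φ[|ln RR|/√V − 1.96], with V = (1/μ_c + k)/n_c + (1/μ_t + k)/n_t.

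Example: 60/60, μ_c = 1.0, RR = 0.6, k = 0.5.

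- p_c = 1 − 1.5^(−2) = 0.556 and p_t = 1 − 1.3^(−2) = 0.408. SE0 = 0.0912 and SE1 = 0.0902. (0.1473 − 0.1788)/0.0902 = −0.35, so power is 36%.
- V = 1.5/60 + 2.167/60 = 0.0611. 0.511/0.247 − 1.96 = 0.11, so power is 54%.

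Repeating this with RR = 0.6, each range running over k = 0.5 to 1.0:

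| Control rate per year | 60/60 chi-squared | 60/60 neg. binomial | 40/80 chi-squared | 40/80 neg. binomial |
|---|---|---|---|---|
| 0.5 | 24-28% | 31-35% | 23-27% | 30-34% |
| 1.0 | 28-36% | 45-54% | 26-33% | 42-52% |
| 1.5 | 28-38% | 53-66% | 25-34% | 50-63% |

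Simulation agrees with the formulas: for the example, 38% for chi-squared against 56% for a rate comparison. At 0.2 to 0.3 events per year the formulas give a gain of only about 0 to 3 points.

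**Step 2: unequal dropout, no true effect.** Assume μ = 1.2 and k = 0.7 in both arms, dropout uniform over the year, and withdrawals without an event scored as event-free.

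- Full year: 1 − 1.84^(−1/0.7) = 0.5815.
- Dropout, averaged over a uniform leaving time: 1 − (1 − 1.84^(−0.4286))/0.36 = 0.3612.
- 5% dropout: 0.95 × 0.5815 + 0.05 × 0.3612 = 57.0% with an event.
- 25% dropout: 0.75 × 0.5815 + 0.25 × 0.3612 = 52.6% with an event.

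With 60/60 the pooled SE is 0.0909, so the 4.4-point shift is 0.485 SE. Type I error ≈ Φ(0.485 − 1.96) + Φ(−0.485 − 1.96) = 7.7%; simulation gives 8.1%. At 5% versus 15% the shift is 2.2 points and the error about 6%. With equal dropout the error stays nominal.

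Across a wider set of simulated settings with equal true rates, 10% versus 30% dropout gave chi-squared rejection of about 6.5-11%. The exposure-adjusted rate ratio stayed at about 0.99-1.03, with rejection of about 5-7%.

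**The case against.** The proportion of patients with an event is a legitimate estimand and matches the article's word risk. A full protocol or analysis plan may say more. Exacerbation is one of several unranked outcomes. All of that is true, but the article positively names the test for this outcome, so this is a stated choice and not a detail left for later. The loss for exacerbations appears in every setting in the table.

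Several stronger readings are tempting, and the documents do not support them:

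- **That the loss applies equally to hospitalization.** At 0.2 to 0.3 events per year it is negligible. If admissions are that rare, Fisher is reasonable, and a negative binomial fit may fail.
- **That the planned analysis is biased.** No dropout figure or direction is given. Daily checklists might cost retention in the intervention arm, but education at each visit and a rented air cleaner might help it. A continuity correction, which the article neither includes nor excludes, lowers the simulated error at 5% versus 25% to 5.9%.
- **That early leavers count as full-year successes.** The article does not define the denominator.
- **That event dates are already captured.** The article says only that exacerbations are checked monthly.
- **That leaving exacerbation history out of the model is an error.** Covariate choice is commonly left to the analysis plan.
- **That a rate model would make the comparison well powered.** At a rate ratio of 0.6 it still reaches only 30-66%.

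**Conclusion.** The point stands for exacerbations. The named test discards information that the monthly checks can supply. Under the stated assumptions the cost is about 7 points of power at 0.5 events per year, 16 to 19 at 1.0 and 24 to 29 at 1.5, over the two dispersion values and both allocation ratios. The direction is firm; the size depends on rates and dispersion that the article does not give. A small part of the gain may reflect the rate comparison rejecting slightly above 5% in some null simulations.

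The bias is a conditional risk. It needs both unequal dropout and withdrawals scored as event-free, and it is modest unless the imbalance is large. For hospitalization the documents support no claim of material power loss. The change is worth making because it is cheap, but the trial does not fail without it.

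**What to change.** For exacerbations, replace the chi-squared or Fisher test with negative binomial regression of the event count, with log(time at risk from randomization) as offset. Adjust for the exacerbation history taken at enrolment and for baseline FEV1 and baseline PM2.5, which the randomization uses. Report the rate ratio with a 95% CI. Give time to first event as supporting analysis and the proportion with any event as a descriptive summary. Start the clock at randomization, because section 2.3 places a month of baseline PM2.5 measurement before it.

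For respiratory hospitalization, use an exact rate comparison on person-time, or keep Fisher and report person-time by arm. Reconcile the 2:1 and 1:1 allocation statements.

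The cost is analysis wording plus data capture at contacts already planned: event counts, event dates and the date of last contact must be recorded. A fallback for sparse data should be specified in advance. The offset corrects only non-informative dropout, so reasons for withdrawal should be reported by arm.
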